## Abstract

**Background:**

Cesarean delivery on maternal request (CDMR) is one of the main reasons for cesarean delivery in Iran, and women often need help in making a decision about the delivery options available to them. The main objective of this study is to evaluate the effect of a computerized decision aid (CDA) system on empowering pregnant women in choosing an appropriate mode of delivery. This CDA contrasts the advantages and disadvantages of vaginal versus cesarean section delivery in terms of their value to the individual woman.

**Methods/Design:**

The protocol concerns a randomized trial study that will be performed among Iranian women. Four hundred pregnant women will be recruited from two private and two public prenatal centers in Mashhad, Iran. They will be randomly assigned to either an intervention or a control group. The designed CDA will be provided to the intervention group, whereas the control group will only receive routine care. The CDA provides educational contents as well as some recommendations. The CDA’s knowledge base is obtained from the results of studies on predictors of cesarean delivery. The CDA’s software will be installed on women’s computers for use at home.

The two primary outcomes for the study are O’Connor’s Decisional Conflict Scale and knowledge as measured by true/false questions. Actual mode of delivery (vaginal versus cesarean) will be compared in the two groups.

**Discussion:**

We investigate the effect of a CDA on empowering pregnant women in terms of reducing their decisional conflict as well as on improving their clinical knowledge pertaining to mode of delivery.

**Trial registration:**

This trial is registered with the Iran Trial Registrar under registration number IRCT2015093010777N4 and registration date 26 October 2015.

## Background

Caesarian section rate in Iran is three times the global average rate. According to a report released by the Iranian Ministry of Health and Medical Education in 2005, caesarian sections constitute 40.7 % of all deliveries in Iran, including 52 % of the deliveries in Tehran (the capital of Iran), of which 64 % are performed in private hospitals [1]. Over the past 30 years, the rate of caesarian sections has been increased in a referral hospital in Tehran from 14.3 % in 1979 to 22.7 % in 1989, 52.5 % in 1999, and 85.3 % in 2009 [2].

A cross-sectional study on 824 pregnant women in Tehran, reported that 72 % of pregnancies with cesarean section were elective. Of these elective pregnancies, 22 % were performed because of a maternal request. Among pregnant women with these requests, 71 % had no explanation for their request. In addition, 65 % of doctors suggested cesarean delivery for their patients without a true medical indication [3]. Results of a study with 350 questionnaires filled out by pregnant women at waiting time for their prenatal visit in eight public health centers and four private offices in Mashhad, Iran, showed that 90 of these pregnant women (26 %) preferred cesarean delivery when a vaginal delivery was appropriate (unpublished observation). These findings are corroborated by studies showing that 70 % of pregnant women in Iran request cesarean section for reasons unrelated to health needs, such as physician's recommendation, personal request, and compliance to the spouse’s preference [4, 5].

Maternal request is one of the main reasons for increasing the rate of cesarean section in Iran. Cesarean delivery on maternal request (CDMR) is defined as the event in which a pregnant woman prefers and requests a cesarean delivery, without maternal or fetal indication, rather than proceeding with a plan for vaginal delivery [6].

The great variance in CDMR across countries suggests that women need help making a decision about the mode of delivery [6–8]. Gynecologists, midwives, and also the family, have significant effect on pregnant women’s decision on mode of delivery [7, 8]. As a result, the decision-making process may be hindered, for example, a disagreement between a physician and the family (unpublished observation).

Despite the importance of involving women in the decision-making process, multiple studies demonstrated that many women have inadequate knowledge to make informed decisions about their pregnancies and maternity cares [3, 8, 9]. Appropriate information and support can provide women with confidence to make their decision, and ultimately, the power to own and justify the decision that they had made. Having the confidence to ask questions, understand clinical information, and communicate delivery mode preferences to the health care professionals, were also considered important factors in making a firm decision by pregnant women [10].

Decision-making is the process of choosing between alternative courses of action (in this study, vaginal delivery versus CDMR). Decision aids (DAs) are increasingly being developed to help patients make informed decisions. Most of the decision aids used in obstetric care are in the form of paper-based information booklet or leaflet [11–15], audio book, or audiotape with an illustrated booklet [16]. Computer-based DAs have also been used in the format of videodiscs [17], CD-ROM programs [18, 19], and Internet sites [20, 21]. Computerized DAs (CDAs) belong to a different group of DAs due to the way they present information that is tailored for each individual [22]. Such aids also reinforce comprehension in a consistent way by providing feedback from the user to the system [23] and using graphic-numeric and text-anchored formats [24].

Some studies have shown evidence supporting the effect of computerized decision aids on improving knowledge of patients and decreasing their decisional conflict [22, 23]. We use the decisional conflict scale (DCS) to measure patients’ perceptions of their uncertainty in choosing a care option, factors contributing to this uncertainty, and effectiveness of decision-making [25].

Decision aids may enhance decision-making by providing a systematic approach to decision-making and enhancing patient autonomy [26, 27]. Specifically, we expect the CDA to improve effective decision-making in pregnant women by clarifying risks and benefits of vaginal versus cesarean delivery, while also considering pregnant women's personal values and their care. One need not expect this improvement to have a negative impact on anxiety.

According to Orem's theory [28], decision-making constitutes a first phase of “deliberative self-care.” People who are competent at self-care and understand entirely the courses of actions are usually open to these actions and receptive to their effectiveness. Hence, improving the decision-making process by decision aids has the potential to enhance self-care. Informed decision-making can potentially reduce the over-use of expensive surgical procedures [29].

The objective of our overall project is to design, construct and evaluate a decision aid to help pregnant women choose mode of delivery. The system’s knowledge-base is obtained from the literature on cesarean delivery predictors. Our hypothesis in this study is that decision aid decreases decisional conflict and increases patient knowledge about cesarean and vaginal delivery modes. Decrease in the frequency of cesarean delivery on maternal request is a secondary expected outcome.

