### Exclusion criteria

Women are excluded if they do not provide a written informed consent, are non-Persian speaking, unable to read and write, or unable to work with a computer. Women whose method of delivery has been predetermined by the physician, based on their clinical condition, are also excluded. In addition, women with miscarriage or other complications are excluded from the study in any group.

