### Outcome

The two primary outcomes for the study are the mean of overall decisional conflict and knowledge scores. The decisional conflict will be measured by O’Connor Decisional Conflict Scale (DCS) [25, 30]. The DCS subscales are secondary outcomes, and they will be compared between the two groups of women. The results of this study will show the specific three affected subscales in the pregnant women's decisional conflict scale. Subscale 1 addresses the uncertainty about choosing among alternatives. Subscale 2 addresses factors contributing to uncertainty, including a - feeling uninformed about the alternatives, benefits and risks; b - being unclear about personal value; c - feeling unsupported in making a choice or pressured to choose on course of action. Finally, subscale 3 addresses the perceived effectiveness of the decision [30].

The DCS scale is assessed for validity and reliability using statistical tests, including factor analysis and Cronbach alpha test. A Persian version of the scale was used in 212 pregnant women in Mashhad, Iran.

Knowledge acquisition will be evaluated by 15 true/false questions that are provided by the researchers. The actual mode of delivery, which will be measured by data obtained from hospital records after the intervention. We will determine the studied pregnant women's decision on mode of delivery before and after intervention and compare the results with the actual delivery mode. We will not evaluate cases with emergency delivery but report on them in the two groups.

The acceptability of the CDA by the enrolled pregnant women in the intervention arm will be assessed by interviewing them and analyzing open-ended comments. Our participants' experiences regarding the use of the decision aids will be reported. Also we will discuss our experience with the CDA’s implementation.

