### Statistical analysis

Differences in the primary outcomes will be analyzed using the “intention-to-treat” principle. The mean decisional conflict score and the mean knowledge score will be compared, using the t-test, to the respective means in the control group. Comparing the actual mode of delivery in the intervention and control groups will be based on hospital maternity records and differences will be tested by the Chi square test. We will calculate the Pearson correlation coefficient between the score of decisional conflict and the mode of delivery.

We will handle missing data by a multiple imputation approach. The multiple imputation procedure replaces each missing value with a set of acceptable values that represent the uncertainty about the right value to impute. These multiply imputed data sets are then analyzed by using standard procedures for complete data and then the results from these analyses are combined.

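### The secondary hypothesis is fewer caesareans on maternal request, but the only stated between-arm delivery test uses a broader proxy, vaginal versus caesarean with emergency deliveries left out

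*Protocol article*

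**What the plan says.** **Hypothesis.** The last paragraph of the Background says: "Decrease in the frequency of cesarean delivery on maternal request is a secondary expected outcome". The Discussion repeats that requests for such caesareans should decline, without giving a size. The Background defines the event as one in which a woman "prefers and requests a cesarean delivery, without maternal or fetal indication, rather than proceeding with a plan for vaginal delivery".

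**Test.** The Abstract (Methods/Design) says: "Actual mode of delivery (vaginal versus cesarean) will be compared in the two groups". Statistical analysis says: "Comparing the actual mode of delivery in the intervention and control groups will be based on hospital maternity records", and that "differences will be tested by the Chi square test". Neither place sorts caesareans by reason or by whether the woman asked for one.

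**Two rules that narrow the comparison.** Outcome says: "We will not evaluate cases with emergency delivery but report on them in the two groups". Exclusion criteria says: "Women whose method of delivery has been predetermined by the physician, based on their clinical condition, are also excluded".

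**Related data.** Outcome also plans to establish each woman's own decision on mode before and after the intervention and to set it against the actual mode. No between-arm test of that decision, or of caesarean on request, is stated.

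**The concern.** The hypothesis concerns one kind of caesarean, and the test counts more than that kind. Three groups cause the difference:

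- Women with no indication at entry (from 28 weeks) who later develop one and have a non-emergency caesarean. They count as events although they did not request it.
- Women whose physician suggested a caesarean without a clinical condition and who did not themselves request it. The entry exclusion covers only modes fixed on clinical grounds.
- Women who have an emergency delivery. They leave the comparison after randomization. If the aid moves a woman from a planned caesarean to attempted vaginal birth and she then has an emergency caesarean, she drops out of the evaluated set. Had she stayed with her plan, she would have counted as a caesarean. This can flatter the aid.

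A null chi-square result would then be weak evidence that requests did not fall, and a positive one would not show directly that they did.

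**Working it through.** **1. The outcomes side by side.**

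| | Hypothesized (Background, Discussion) | Tested (Abstract, Outcome, Statistical analysis) |
|---|---|---|
| Event | Caesarean requested by the woman, no maternal or fetal indication | Any evaluated caesarean |
| Classified by request or indication | Yes, by definition | No |
| Emergency deliveries | Non-events | Not evaluated, only reported by group |
| Indications known at entry | Not events | Excluded at entry |
| Non-emergency indications arising later | Not events | Events |

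**2. How far the two can differ.** In the Tehran study cited in the Background, 72% of caesareans were elective, and 22% of those "were performed because of a maternal request". That is 0.72 × 0.22 = 15.8% of all caesareans, and 78% of the elective ones were not on request. Those women were not selected as in this trial. The exclusion of clinically predetermined modes should raise the request share here, by an amount the article does not give.

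**3. Illustration of dilution.** The article states no rate, effect size or power for delivery mode (Sample size rests on decisional conflict), so there is no figure to reproduce. Assumptions:

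- n = 200 evaluable women per arm; two-sided 5%.
- Request caesareans occur in a share c of control births and are halved by the aid.
- Other evaluated caesareans occur in a share o of births, the same in both arms.
- c = 26% is borrowed from the Mashhad questionnaire study in the Background (90 of 350 women preferred caesarean when vaginal delivery was appropriate). It is a preference, not a delivery rate. c = 15% is a lower assumed value.
- o = 10%, 20% or 30% is assumed.

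Power = Φ{(d − 1.96·SE0)/SE1}, where d = p1 − p2, SE0 = √[2·p̄(1 − p̄)/n], SE1 = √[(p1(1 − p1) + p2(1 − p2))/n], and p̄ is the mean of p1 and p2. For request caesareans, p1 = c and p2 = c/2. For any caesarean, p1 = c + o and p2 = c/2 + o. The difference d is c/2 either way; only the variance changes.

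Request caesareans, c = 26%: p1 = 0.26, p2 = 0.13, SE0 = 0.0396, SE1 = 0.0391. (0.13 − 0.0777)/0.0391 = 1.34, power 91%.

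Any caesarean, c = 26%, o = 20%: p1 = 0.46, p2 = 0.33, SE0 = 0.0489, SE1 = 0.0485. (0.13 − 0.0958)/0.0485 = 0.71, power 76%.

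| c | Request caesareans | Any, o = 10% | Any, o = 20% | Any, o = 30% |
|---|---|---|---|---|
| 26% | 91% | 82% | 76% | 74% |
| 15% | 66% | 45% | 37% | 33% |

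With o = 0 the two analyses coincide. The loss is moderate when requests are common and larger when they are rare.

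**The case against.** The strongest reply is that the plan already comes close. Emergency deliveries are outside the evaluation and clinically predetermined modes are excluded, so what remains is roughly non-emergency caesarean in women without an indication at entry. The Background itself equates the choice under study with vaginal delivery versus caesarean on request. Actual mode is objective, while recorded indication can be wrong. The stated decision is collected and bears directly on requests. Delivery mode is secondary, and coding detail may sit in a fuller document.

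Much of this stands, and it rules out several stronger readings that a reader might infer:

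- *That the test counts all caesareans, or does not measure the hypothesized outcome.* The emergency rule and the entry exclusion contradict this. It is an imperfect proxy.
- *That the trial cannot answer its secondary question.* The records and the stated decision are planned data; what is absent is a between-arm comparison built on them.
- *That power is only about 10%.* Applying the 15.8% share to the 40.7% national caesarean rate gives 6.4% of births on request. Halving that leaves 40.7% versus 37.5% on all caesareans, power 10%, against 32% on request caesareans. Those inputs describe unselected women, emergencies included, not this trial's population.
- *That a positive result could simply reflect physicians' decisions.* Study design says the gynecologists are unaware of allocation, so differences in their decisions by arm would most plausibly arise through the women.

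What the reply does not remove is that the article names one outcome and fixes its test on another. That is a mismatch in stated text, not detail left for later. The entry exclusion cannot act on indications that arise after entry, and the emergency rule brings its own post-randomization problem.

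**Conclusion.** The point holds in a limited form. The stated secondary hypothesis concerns caesarean on maternal request, and the only stated between-arm delivery test is on a broader proxy, further altered by dropping emergency deliveries after randomization. The size of the dilution cannot be derived from the documents, because neither the request share among eligible women nor the rate of other non-emergency caesareans is given. Under the assumptions shown, power falls from about 91% to 74–82% when requests are 26% of births, and from 66% to 33–45% when they are 15%. These figures rest on an assumed halving of requests, no effect on other caesareans, and 200 evaluable women per arm. The two primary outcomes and the sample size basis are untouched. The mismatch should be corrected, but it affects only the reading of the delivery result.

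**What to change.** - Add a secondary outcome, caesarean on maternal request: a caesarean with no maternal or fetal indication in the records **and** a stated decision for caesarean at the 38-week questionnaire. Both parts are needed, because absence of an indication alone would also count caesareans suggested by the physician without a request.
- Code the indication with allocation masked.
- Compare the outcome by arm with all randomized women in the denominator and all other births, including emergencies, as non-events.
- Keep actual mode of delivery as a second delivery outcome, counting any caesarean with emergencies included.
- At minimum, reword the secondary hypothesis as caesarean delivery so that it matches the test.

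**Cost.** One more item is extracted from hospital and clinic records that Data collection and Outcome already use, plus a change of analysis wording. Some recorded indications will be misclassified. The stated decision comes from women who know their allocation, and a rule is needed for those who deliver before the 38-week questionnaire. Keeping any caesarean alongside gives an objective check on both.

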## Methods/design

### Design of the intervention

We developed a decision aid for the mode of delivery using the three steps of the Ottawa Decision Support framework: identifying needs, providing decision support and evaluating decision support. A cross sectional study was done to reveal pregnant women’s preferences and concerns about childbirth. We specified the variables associated with cesarean delivery in pregnant women based on a literature study and a field study (under publication). The need for a decision aid was identified following another literature review and by forming focus groups with experts.

Based on the identified needs in the first step, we developed a computerized decision aid (CDA) system. This computer-based decision support system is an application that pregnant women can use alone or with their families. The program will be installed on a personal computer and/or laptop of pregnant women who are recruited for the intervention group, to be used at home. Capabilities of the installed software include the following:Information retrieval: A list is available of topics that contain information about the types of delivery. Hyperlinks to educational content are also placed in the decision-support section. The included information explains the tradeoffs between vaginal delivery versus CDMR.Clinical data entry: Two categories of information can be entered into the computer by pregnant women. These are listed below.General information (for example, age, gestational age, weight, and height) and health history (for example, parity, history of smoking, drug abuse, and anxiety).Response to 15 statements organized in two categories pertaining to 1) possible reasons for seeking CDMR, such as desire to plan or avoid unplanned cesarean section, and 2) factors that may encourage the selection of natural delivery, such as not requiring anesthesia, surgery or shorter rest after delivery.Decision-support tool: this is an interactive computerized module for supporting the selection of delivery mode. Women are given information about the outcomes associated with vaginal delivery, elective caesarean section, and emergency caesarean section. They can include their personal preferences for possible outcomes by answering questions about 15 statements (section b. clinical data entry). The software program combines the answers and represents the overall results about vaginal delivery versus cesarean section. We also provide an interactive self-assessment and feedback module to educate and correct their misunderstandings about delivery modes.

### Ethics

The Ethical committee of Mashhad University of Medical Sciences has granted ethics approval to conduct this trial (326955, 30^th^ August 2015). A signed consent form is obtained from all participants in this trial at the time of recruitment.

### Setting for the trial

The study will be conducted in the primary health care setting of Mashhad, the second largest city in Iran with approximately three million residents. All women who plan to give birth at the two public health care centers and the two private offices can participate in this study if they sign the consent form. The selection of these facilities is based on their readiness for project implementation. Six gynecologists are practicing at the two public health care centers offices, and they see about 1,700 pregnant women per month (250 to 300 returning patients). The two gynecologists in the private offices see about 700 pregnant women per month (100 to 150 returning patients).

### Study design

This study follows is a randomized controlled trial design. Subjects (pregnant women) are the unit of randomization; they are randomly allocated to each arm of the study. Both the intervention and control group will receive usual care, but the intervention group will also receive the CDA. An independent researcher will centrally perform the randomization by using the computer program on www.randomization.com. Block randomization will be applied to ensure equal group sizes within each center. Because the study is not blinded, we use blocked randomization with randomly selected block sizes of two and four. For each center, the independent researcher will prepare opaque, sequentially numbered, and sealed coded envelopes, with a note for either the decision aid use or not. At each center, the clinic secretary will check eligibility of each pregnant woman visiting the clinic and, if eligible, will provide her with an explanation of the aims and scope of the study and will orally invite her to participate in the study. If the invitee accepts the invitation, then she will be asked to sign the informed consent form. Then the secretary writes the woman’s name and phone number on the next closed envelope. At the end of the day, all envelopes, unopened as of yet, are collected by a research assistant. At the university, this researcher assistant opens the envelopes and allocates the participants of that day to the decision aid or control group. After group allocation, the research assistant will call the participants by phone. Those in the intervention arm will be invited to a software educational session (consisting of 10 women in total) and invited to fill in the paper questionnaires. Those in the control arm will be invited to only fill in the questionnaires. All participants (in the intervention and control arms) will be invited to fill in the questionnaires again two weeks before the expected date of delivery. Blinding of researchers and women is not practical in this study, but the gynecologists are unaware of the patient allocations.

The duration of the intervention is considered from recruitment to the time of delivery. The evaluation of the intervention will be performed at 38 weeks of gestation and before delivery. We will report all cases due to premature delivery.

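### Group software training is given in the intervention arm only, so the trial tests the CDA with that training, and the planned t-test takes no account of possible correlation within training sessions

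*Protocol article*

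**What the plan says.** In the protocol article, the Study design section summarises the contrast in one sentence: "Both the intervention and control group will receive usual care, but the intervention group will also receive the CDA". The abstract gives the same picture: "The designed CDA will be provided to the intervention group, whereas the control group will only receive routine care".

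Further on, Study design describes what happens after allocation. For the aid arm: "Those in the intervention arm will be invited to a software educational session (consisting of 10 women in total". For the other arm: "Those in the control arm will be invited to only fill in the questionnaires".

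Design of the intervention describes the CDA by its software functions, as "an application that pregnant women can use alone or with their families", installed for use at home. The training session is not listed there. The Discussion, in the abstract and in the main text, attributes the expected effect to the CDA and does not mention the session.

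The primary analysis is fixed in Statistical analysis: "The mean decisional conflict score and the mean knowledge score will be compared, using the t-test, to the respective means in the control group". Neither that section nor Sample size mentions training groups.

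**The concern.** Two things follow from training one arm in groups.

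First, the arms differ by the software together with a group session. A clinic that later supplies only the home software would not be delivering what was tested. The design has no means of separating the two parts, so the conclusion should name both.

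Second, women who share a session share its trainer, its questions and one another's company. Their later scores may be more alike than those of women trained in different sessions. Control women have no such grouping. A t-test that assumes independence would then understate the standard error of the difference, and the real false-positive rate would exceed the stated 5%. The test is named in the article, so this is not a detail left to a plan that is not shown.

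**Working it through.** **Inputs from the protocol article**
- 200 women per arm, 80% power, 5% type I error, SD 17.6, mean 33.6 (Sample size). Two-sided testing is assumed, as sidedness is not stated.
- Sessions of 10 women, intervention arm only (Study design).

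**Assumptions**
- 200 / 10 = 20 full sessions. The number of sessions is not stated, and women are only invited.
- Equal total variance in the two arms.
- ICC of 0.01, 0.02, 0.05 or 0.10. The documents give none, so a range is shown.

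**Step 1. The plan's own sample size.** The 15% is worded as an absolute fall in a rate. Read as two proportions 15 points apart, with control rates from 30% to 70%, it needs 242 to 348 women without continuity correction and 268 to 374 with it. Read as 15 DCS points, it needs 44. Neither gives 400. Read as a relative fall in the mean, it is 0.15 × 33.6 = 5.04 points:

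n per arm = 2 × [17.6 × (1.960 + 0.842) / 5.04]² ≈ 191.4, so 192 per arm, 384 in total.

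With the difference rounded to 5 points the total is 390. At 200 per arm and 5.04 points, power is 81.7%. This reading comes close to the stated design and is used below for power. The type I error figures do not depend on it.

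**Step 2. Type I error of the t-test as planned.**
- Design effect in the intervention arm: DE = 1 + (10 − 1) × ICC.
- True SE divided by the SE assumed by the t-test: R = √[(1 + DE) / 2].
- Actual type I error = 2 × [1 − Φ(1.96 / R)].

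Example at ICC 0.05: DE = 1.45; R = √(2.45 / 2) = 1.107; 1.96 / 1.107 = 1.771; error ≈ 7.7%.

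**Step 3. Power once the clustering is allowed for.**
- SE = 17.6 × √(DE/200 + 1/200).
- Power = Φ(5.04 / SE − 1.96).

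Example at ICC 0.05: SE = 17.6 × √(2.45 / 200) = 1.948; 5.04 / 1.948 − 1.96 = 0.627; power ≈ 73.5%.

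| ICC | DE | SE ratio R | Type I error, plain t-test | Power at 200 per arm, clustering allowed for | Total for 80% power |
|---|---|---|---|---|---|
| 0 | 1.00 | 1.00 | 5.0% | 81.7% | 384 |
| 0.01 | 1.09 | 1.02 | 5.5% | 80.0% | 402 |
| 0.02 | 1.18 | 1.04 | 6.1% | 78.3% | 418 |
| 0.05 | 1.45 | 1.11 | 7.7% | 73.5% | 470 |
| 0.10 | 1.90 | 1.20 | 10.4% | 66.2% | 556 |

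These are normal approximations that ignore center.

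**The case against.** A reader might infer that the session is an undeclared source of decisional support, and that the trial therefore cannot say anything about the CDA. The DCS does include an item group on "feeling unsupported in making a choice or pressured to choose on course of action", which group contact could in principle move. The documents do not support going that far. The session is disclosed in the same section as the contrast and is called software education. The Discussion lists computer literacy and troubleshooting as barriers, so training in use of the program is the natural reading. Nothing says that the session offers counselling or discussion of preferences. The randomized intention-to-treat comparison remains a valid test of the aid as delivered. What stands is that the summary sentences leave out part of what is delivered. The lack of a session script is not a finding, because a condensed article commonly leaves such detail to the full protocol.

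A reader might also take it as established that outcomes are clustered. The design only makes this possible. There is one session, then use at home alone or with family, and outcomes are measured at 38 weeks, up to 10 weeks after enrolment at 28 weeks. The ICC could be small, and at 0.01 to 0.02 the excess error is minor.

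It is also fair to say that both arms share four centers. With randomization blocked within center, an unadjusted t-test tends to be conservative if centers differ, which would offset part of the inflation. The size of that offset cannot be derived from the documents. It is a reason to put center in the model, because sessions filled from a single center would otherwise let the session effect absorb differences that exist in both arms.

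**Conclusion.** The point holds in a limited form, as an inexpensive improvement. The trial tests the CDA with group software training against usual care, and the text should say so. The planned t-test has no protection against correlation within sessions. Its true type I error would be about 5.5% to 10.4% for ICCs from 0.01 to 0.10. This rests on 20 full sessions of 10, equal variances, no offset from center differences, and an ICC that the documents do not give. The effect is trivial at the low end of that range and material from about 0.05 upwards. The wording of the session size is loose, but groups of 10 is the natural reading. The validity of the randomized comparison of the package is not in doubt.

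**What to change.** 1. **Record the session.** Enter a session number for each intervention woman at the time. It may not be recoverable later.
2. **Analyse accordingly.** Compare DCS and knowledge scores with a partially nested mixed model: a random session effect in the intervention arm only, and each control woman as her own cluster. Equivalent cluster-robust standard errors with a small-sample correction would also serve, since there are only about 20 sessions. Include center as a fixed effect, because randomization is blocked within center. Women who attend no session stay in their allocated arm, each as her own cluster.
3. **Name the package.** In the abstract, Study design and Discussion, describe the intervention as the CDA with group software training, and limit the conclusion to that.

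The cost is one data field, a revised model statement and a few changes of wording. No extra visits are needed. The statistical price is wider intervals if correlation is present. With 400 women and a difference of about 5 DCS points, power falls below the stated 80% once the ICC exceeds about 0.01, and is about 73.5% at 0.05. Restoring 80% at that ICC would take about 470 women, so the sponsor should either accept the lower power or decide on a larger sample before recruitment ends.
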